| --- | --- |

1. **Study design**

| **3.1**  **a. General description of the study design** | This research project will use the data infrastructure Extramural Leiden Academic Network (ELAN).  ELAN provides access to and the use of pseudonymized healthcare data from various cooperating partners such as healthcare data of general practitioners. The study period concedes 2014-2024.  ***Question***  Is antibiotic use associated with increased risk for urinary tract infection in adults?  Further explorations will be done to what extent the increased UTI risk of antibiotic use holds for:   - Different antibiotics or antibiotic classes - Men versus women - Post- versus Premenopausal women - Indication for antibiotic treatment (excluding UTI’s)   A self-controlled cases series (SCCS) design will be employed to establish the risk for developing an UTI within 3 months after antibiotic treatment compared to patients with an UTI who did not receive an antibiotic treatment. With the SCCS design, patients will be their own control.  The primary endpoint is risk of a UTI within 3 months after initiation of antibiotic treatment computed as an odds ratio.  An antibiotic treatment is defined as the exposure. An UTI between 2 weeks and 3 months after antibiotic treatment is defined as an event. The first 2 weeks after start of the treatment, patients are still somewhat protected by the antibiotic use against a new infection. And if a new antibiotic treatment is needed within 2 weeks after start of treatment, this is considered as treatment failure of the initial treatment.  Descriptive analysis will be performed for exposures, outcomes and covariables for the whole population of analysis and stratified by antibiotic use or not.  Multivariable logistic regression analysis will be performed to assess whether there is an association of antibiotic use with developing a UTI within 3 months after initiation of treatment. First a crude model will be used followed by confounder adjusted models. Confounders are season variability (Winter, spring, summer and autumn) and risk factors for UTI and selected based on theory or literature (Tj VanderWeele 2019). Risk factors are a history of an UTI, urine incontinence, urolithiasis, pregnancy, urine catheter, anatomical / functional abnormality urinary tract, immunocompromising comorbidities such as HIV/AIDS ,Type 2 Diabetes Mellitus.  **Subgroup analysis**  Subsequently, subgroup analysis will be performed to examine whether the association differs upon specific type of antibiotic treatment. For each subgroup, we will calculate an odds ratio for an UTI after antibiotic treatment. Subgroups are antibiotic(group)s, gender and age, type of infection and social determinants .  *Most used antibiotic(group)s in primary care*:   - Amoxicillin - Amoxicillin/clavulanic acid - Flucloxacillin - Tetracyclines - Macrolides - Fluoroquinolones - Trimethoprim - Co-trimoxazole - Fosfomycin - Nitrofurantoin   *Type of infection*   - All infections - UTI - non-UTI (all other infections)   *Gender and age*   - Men - Premenopausal women, defined as < 50 years of age - Postmenopausal women, defined as ≥ 50 years of age   *Social determinants*   - Socio-economic status (SES) - Migrant background |

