| --- | --- |
| **3.2**  **a. When will the study be conducted?**  **b. What is the intended end date of the study?** | The research will be performed as part of a MSc. Internship ([name]) in the period between February 2025 and June 2025.  Month 1 – Literature research, writing the introduction, first part of data preparation.  Month 2 – Writing the introduction and methodology, second part of data preparation.  Month 3 – Completing the introduction, methodology and data preparation, start of data analysis.  Month 4 – Completing the data analysis and writing the results.  Month 5 – Writing the report, focusing on the discussion.  The end date is July 2025. |
| **3.3**  **Does the study involve exclusively existing (patient) data (retrospective) and not data yet to be generated (prospective)?** | This study includes already existing data only, and is thus retrospective (see also 3.1). |
| **3.4**  **What type of data will be used for the research?** | Pseudonymized routine care patient data from GP practices participating in ELAN. |
| **3.5**  **If information from patient records is used: describe what type of information is involved.** | The dataset from ELAN contains data over a period of 10 years and includes:   - Number of all included patients in ELAN per year - All patients with an UTI   - ICPC code U70, U71, including subcodes   - Date of registration with GP office - Antibiotic prescriptions ATC J01 for all patients with an UTI   - Corresponding medical diagnosis with the antibiotic prescription by ICPC code   - Details on the antibiotic prescription (name of antibiotic, dose and duration) - Characteristics of included patients   - Year of birth   - Year of death   - Sex   - Referral to urologist for recurrent UTIs   - Risk factors for an UTI     - History of UTI ICPC code U70, U71     - Urine incontinence ICPC code U04     - Urolithiasis ICPC code U95     - Urine catheter ICPC code U28     - Anatomical / functional abnormality urinary tract ICPC code U85     - Type 2 Diabetes Mellitus ICPC code T90.02     - Prostate hypertrophy ICPC codes Y06, Y85     - Medication use for miction problems with ATC codes     - G04BD     - G04C     - Social economic status     - Migrant background |
| **3.6**  **To which time period do the data relate?** | The period between 2014 and 2024 |

1. **Data storage and privacy**

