| **6.1**  **a. Primary outcome**  **b. Secondary outcome** | ***Primary outcome***  What is the association of antibiotic use for any infection with risk for urinary tract infection in adults?   - Odds ratio for an UTI after antibiotic use in the preceding 3 months   - Per infection group, antibiotic for     - All infections     - An UTI     - An infection expect UTI’s   - Per antibiotic (group)   - Per patient group     - Men     - Women < 50 years of age     - Women ≥ 50 years of age   - Social determinants     - SES     - Migrant background   - Combinations of each subgroup   ***Secondary outcome***   - Hazard ratio for an UTI after antibiotic use in the preceding 3 months   - Per infection group, antibiotic for     - All infections     - UTI     - non-UTI   - Per antibiotic group   - Per patient group     - Men     - Women < 50 years of age     - Women ≥ 50 years of age   - Social determinants     - SES     - Migrant background   - Combination of each subgroup - Incidence of an UTI per month |
| --- | --- |
| **6.2**  **a. Statistical analysis primary outcome**    **b. Statistical analysis secondary outcome** | ***Primary outcome***  The Odds ratio for an UTI after antibiotic treatment the preceding 3 months will be calculated through a logistic regression model.  Risk factors and season variability are defined as confounders in this logistic regression model. Risk factors are a history of an UTI, urine incontinence, urolithiasis, pregnancy, urine catheter, anatomical / functional abnormality urinary tract and Type 2 Diabetes Mellitus. An Odds ratio for an UTI will be attributed to each confounder based on a critical literature appraisal.  ***Secondary outcome***  Cox proportional hazard regression models will be used to examine the associations between an UTI after antibiotic treatment the preceding 3 months.  Survival time (in days) was defined as the period between 14 days after the start of the antibiotic treatment and an UTI. The hazard ratio will be adjusted with the previous described confounders (see primary outcome).  The incidence of each UTI will be calculated for each month during 10 years to examine the season variability. |

1. **Appendices and references**

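### The protocol names a self-controlled design but fixes unconditional logistic and Cox models with no unit of analysis, so the odds ratio is not within-person and its standard error is unreliable in either direction

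*Protocol*

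**What the plan says.** **Design.** Section 3.1 names a self-controlled case series and adds: "With the SCCS design, patients will be their own control". It sets the exposure at the level of the course: "An antibiotic treatment is defined as the exposure". The event is a UTI from 2 weeks to 3 months later. The same section also words the comparison as one against UTI patients who were not given an antibiotic, which is a contrast between people.

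**Data.** Section 3.5 states: "The dataset from ELAN contains data over a period of 10 years". It lists "Antibiotic prescriptions ATC J01 for all patients with an UTI". No limit to one course per patient is given. Section 5.2 has a 1-year wash-out for UTI events.

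**Models.** Section 3.1: "Multivariable logistic regression analysis will be performed to assess whether there is an association of antibiotic use". Section 6.2, primary outcome: the odds ratio "will be calculated through a logistic regression model". Section 6.2, secondary outcome: "Cox proportional hazard regression models will be used", with the clock defined as follows: "Survival time (in days) was defined as the period between 14 days after the start of the antibiotic treatment and an UTI".

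Neither section mentions a conditional likelihood, a patient stratum, a random effect or frailty, or a clustered variance. Neither says whether a record is a patient, a course, a period or a UTI.

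**The concern.** In a self-controlled case series, each patient's exposed time is compared with the same patient's unexposed time. Stable patient characteristics then cancel, whether or not they were measured. The cancelling comes from conditioning on the patient in the model. An ordinary logistic or Cox model on pooled records does not condition, so the contrast becomes a mixture of within-patient and between-patient differences. Patients who are prone to UTI for stable reasons that are not recorded, and who also receive more antibiotics, would then push the odds ratio upwards.

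The second issue is dependence. If several courses or periods of one patient enter, their outcomes are correlated, and the default standard error ignores this. The resulting error carries into the estimates by antibiotic group, indication, patient group, social determinant and their combinations in section 6.1.

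**Working it through.** **1. Do several records per patient arise?** The exposure is a course, the data span about 10 years, and no section limits courses to one per patient. The wash-out in section 5.2 spaces UTI events but does not reduce them to one. Section 6.1 also asks for an estimate for antibiotics given for a UTI, which needs an index UTI and a later UTI in the same person. Several records per patient is therefore the natural reading, though the protocol does not say so outright.

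**2. Inputs for the size.** The protocol states no sample size, event count, number of records per patient or correlation, so there is no figure to reproduce. Everything below is assumed:
- m, records per patient: 3 as the base case, 2 and 10 as the range.
- ρy, within-patient correlation of the outcome: 0.1 to 0.3.
- ρx, within-patient correlation of the exposure: from −1/(m−1), when every patient has the same number of exposed periods, up to 1, when exposure never changes within a patient.

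**3. Formulas.** Design effect DE = 1 + (m−1)·ρx·ρy. True SE / default SE = √DE. Coverage of a nominal 95% interval = 2Φ(1.96/√DE) − 1.

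**4. Results for m = 3.**

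| Exposure pattern | ρx | DE (ρy 0.1; 0.3) | SE factor | Coverage |
|---|---|---|---|---|
| Constant within patient | 1 | 1.20; 1.60 | 1.10; 1.26 | 93%; 88% |
| Partly clustered | 0.3 | 1.06; 1.18 | 1.03; 1.09 | 94%; 93% |
| Unrelated between records | 0 | 1.00; 1.00 | 1.00; 1.00 | 95%; 95% |
| Same number exposed in every patient | −0.5 | 0.90; 0.70 | 0.95; 0.84 | 96%; 98% |

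Example, second row, ρy = 0.3: 1 + 2 × 0.3 × 0.3 = 1.18; √1.18 = 1.086; 1.96/1.086 = 1.80; coverage 93%. Last row: ρx = −1/(3−1) = −0.5, so DE = 1 − ρy.

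**5. Range over m.** At ρx = 0.3 the SE factor is 1.015 to 1.044 for m = 2 and 1.13 to 1.35 for m = 10. At ρx = 1 it is 1.05 to 1.14 for m = 2 and 1.38 to 1.92 for m = 10.

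**6. Simulation check, including the point estimate.** Assumed: 1,500 patients with 10 periods each, baseline logit −2.5, a within-patient odds ratio of 1.5, a normal patient effect with SD 1.0 or 1.5, 300 replicates, and unadjusted pooled logistic regression. Coverage is of the estimator's own mean.

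| Exposure pattern | Patient-clustered SE / default SE (SD 1.0; 1.5) | Coverage of default interval | Pooled OR |
|---|---|---|---|
| Constant within patient | 1.40; 1.74 | 85%; 74% | 1.43; 1.37 |
| Partly clustered | 1.07; 1.15 | 95%; 91% | 1.45; 1.37 |
| Independent between periods (SD 1.0 only) | 1.00 | 94% | 1.44 |
| 3 of 10 periods exposed in every patient | 0.95; 0.88 | 98%; 98% | 1.45; 1.37 |

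The pooled odds ratios of 1.37 to 1.45 lie below 1.5 because an odds ratio averaged over patients differs from the one within a patient. That is a change of estimand, not confounding. In a further run with SD 1.0, the unmeasured patient effect also raised the chance of antibiotic use (exposure logit −1.0 + 0.7 times the patient effect). The pooled odds ratio was then 2.58, and no default interval contained 1.5. In that run the clustered SE was only 1.06 times the default SE, so correcting the variance would not have repaired the estimate.

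**The case against.** The strongest case on the other side has four parts.

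*The protocol never says that every course and every UTI enters as a separate record.* Correct. Defining the exposure as a treatment does not fix the unit of analysis, and the wash-out would remove many closely spaced recurrences. Several records per patient is an inference from sections 3.1, 3.5 and 6.1. It is a fair one, and the missing unit of analysis is part of the problem.

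*A reader might infer that the confidence intervals are simply too narrow, with too many false positives in the subgroups.* The protocol does not support that. The direction depends on how exposure is spread within patients. Intervals are too narrow when exposure clusters, as under the between-patient comparator that section 3.1 also words. They are about right or too wide in the within-patient layout that the named design implies.

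*The familiar formula 1 + (m−1)ρ overstates the effect.* This also stands. It assumes exposure that is constant within the patient, which antibiotic use in the preceding 3 months is not over 10 years. Its results are an upper bound.

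*Variance estimation belongs in the statistical analysis plan, which is not at hand.* For a clustered-variance option alone, this is fair. It does not cover the main point: the protocol itself chose both the design and the models. A self-controlled design paired with unconditional models is a mismatch in the protocol text, not a detail left open.

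**Conclusion.** The point holds as a mismatch between design and model. Fitting the models as named would discard the own-control comparison, so stable differences between patients that the listed confounders do not capture can bias the odds ratio. The standard errors would also be unreliable, in a direction that the protocol does not determine.

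The size cannot be derived from the protocol. With 3 records per patient and an outcome correlation of 0.1 to 0.3, coverage is about 94% to 93% at an exposure correlation of 0.3 and 93% to 88% at the upper bound of 1. It is slightly above 95% in a balanced within-patient layout. The simulated odds ratio of 2.58 against 1.5 illustrates how far the estimate can move under one assumed strength of unmeasured confounding, without the planned covariate adjustment. It does not predict this study's result. On these figures the threat to the estimate is potentially larger than the threat to the interval. The protocol should be changed before the analysis is run, but the point does not show that any particular interval will be too narrow.

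**What to change.** In section 6.2, with matching wording in section 3.1:

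1. State the unit of analysis, and whether all courses and all UTIs of a patient enter or only the first of each.
2. Estimate the primary outcome conditional on the patient: conditional Poisson regression for the case series, or conditional logistic regression.
3. For any between-patient logistic or Cox model that is kept, use patient-clustered robust variance or a shared frailty. Say that clustered variance alone does not restore the own-control comparison.
4. Reconcile the between-patient comparator in section 3.1 with the self-controlled design.

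The cost is a few lines of text and a little more analysis work with standard software; no new data are needed. Some intervals may widen. Conditional Poisson regression yields a rate ratio, so the effect measure in sections 3.1 and 6.1 would need rewording; conditional logistic regression keeps an odds ratio. Covariates that do not change within a patient drop out of a conditional model, while season and other time-varying factors remain. A standard case series also assumes that an event does not alter later exposure. Because a UTI usually prompts an antibiotic, section 6.2 should say how this is handled.

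### The models pool 2014-2024 but handle calendar time only through a four-level season; adding calendar year is a cheap safeguard, chiefly for the per-antibiotic estimates

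*Protocol*

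**What the plan says.** Protocol sections 3.1 and 3.6 set the data window: "The study period concedes 2014-2024" and "The period between 2014 and 2024".

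The adjustment set is named twice. Section 3.1: "Confounders are season variability (Winter, spring, summer and autumn) and risk factors for UTI". Section 6.2, for the logistic model: "Risk factors and season variability are defined as confounders in this logistic regression model", followed by the clinical items: "Risk factors are a history of an UTI, urine incontinence, urolithiasis, pregnancy, urine catheter, anatomical / functional abnormality urinary tract and Type 2 Diabetes Mellitus". None of these items is a calendar-time term or stands in for one.

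The Cox model takes over the same set: "The hazard ratio will be adjusted with the previous described confounders (see primary outcome". Its clock is time since treatment: "Survival time (in days) was defined as the period between 14 days after the start of the antibiotic treatment and an UTI".

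Sections 3.1 and 6.1 plan separate estimates for individual antibiotics or antibiotic groups (ten are listed in 3.1). The only other use of calendar time is a monthly UTI incidence in 6.2. Its stated purpose is to look at season, and it does not feed into the models.

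**The concern.** The protocol treats calendar time as a confounder, but models only the part that repeats every year. A winter in 2014 and a winter in 2024 get the same adjustment. The Cox baseline hazard does not help, because it runs on days since treatment and not on calendar date.

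Suppose a drug is prescribed more in the later years, and UTIs also occur or are recorded more often in those years. The drug's exposed time then lies mostly in years with more UTIs, and its comparison time is spread more evenly. The pooled odds ratio moves away from the true value even if the drug does nothing. If the drug's use falls instead, the bias goes the other way. Single drugs can change in use far more than antibiotics as a whole, so the per-antibiotic estimates are the more exposed. What is at stake there is whether a modest association can be told apart from a difference between eras.

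**Working it through.** The protocol gives no trend, sample size or effect size, so there is no figure of its own to reproduce. What follows is an illustration, and all drift sizes are assumptions.

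**Inputs.** From the protocol: the 2014-2024 window (11 calendar years if both ends count, or 132 months), four seasons, and a logistic model. Assumed: true odds ratio 1.00; 3% of person-months exposed at the start; 1% monthly UTI risk at the start; use changing smoothly by a factor u over the period and UTI occurrence or recording by a factor k.

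**Formula.** With t running from 0 to 1, exposure prevalence is e(t) = 0.03·u^t and monthly risk is r(t) = 0.01·k^t, the same for exposed and unexposed. The pooled risk ratio is [Σe·r / Σe] ÷ [Σ(1−e)·r / Σ(1−e)]. It differs from 1 only when both u and k differ from 1.

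**By hand, u = 2, k = 1.3** (risks relative to the start).
- Mean risk in exposed time: [(2.6−1)/ln 2.6] ÷ [(2−1)/ln 2] = 1.6745/1.4427 = 1.1607.
- Mean risk over all time: 0.3/ln 1.3 = 1.1434.
- Mean exposure: 0.03 × 1.4427 = 0.0433.
- Mean risk in unexposed time: (1.1434 − 0.0433 × 1.1607)/0.9567 = 1.1427.
- Ratio: 1.1607/1.1427 = 1.016.

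**Weighted logistic fits on expected counts over 132 months:**

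| Change in use (u) | Change in UTI recording (k) | OR, season only | OR, season + year |
|---|---|---|---|
| 2 | 1.3 | 1.016 | 1.000 |
| 1/2 | 1.3 | 0.984 | 1.000 |
| 3 | 1.3 | 1.026 | 1.000 |
| 3 | 1.5 | 1.040 | 1.000 |
| 1/3 | 1.5 | 0.963 | 1.000 |
| 5 | 1.5 | 1.058 | 1.000 |
| 5 | 2 | 1.100 | 1.000 |

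With u = 1 or k = 1 the season-only odds ratio is 1.000.

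**Second method.** Take 11 equal-sized years, 2% exposed in the first year, and compare the pooled odds ratio with a Mantel-Haenszel odds ratio stratified by year. With a true value of 1.00, the pooled odds ratio is 1.005 to 1.016 when use rises 1.25-fold and UTI odds rise 1.25- to 2-fold. It is 1.10 for a fourfold rise in use with doubled UTI odds, and 0.91 for a fall in use to a quarter with doubled UTI odds. With a true value of 1.30, the same two extremes give 1.43 and 1.18. Stratifying by year returns the true value each time.

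**Within-person version.** Section 3.1 names a self-controlled design, so the 132-month scenarios were also run with each person compared only with their own time. Follow-up windows of equal length were spread over the period (the lengths are assumed).

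| Follow-up | u = 5, k = 1.5 | u = 5, k = 2 |
|---|---|---|
| 2 years | 1.002 | 1.003 |
| 4 years | 1.008 | 1.014 |
| 6 years | 1.018 | 1.030 |
| 11 years | 1.058 | 1.100 |

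Nothing was computed for the Cox model.

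**The case against.** The strongest objection is that drift is not documented. No section reports a trend in UTI recording, in prescribing or in the warehouse's coverage, and bias needs drift in both exposure and outcome. A reader might infer from "Number of all included patients in ELAN per year" in section 3.5 that ascertainment is known to change. That item is only a requested yearly denominator and does not support the inference. Section 2.1 says UTI incidence rises with age, and within one patient age and year advance together, but this speaks only to the outcome side. This objection stands, so the point has to be conditional.

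Second, the primary question concerns antibiotics for any infection, where plausible drift gives 2% or less. The 6-10% figures need a 5-fold change in one drug together with a 1.5- to 2-fold change in recording. This also stands.

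Third, true self-control removes most of the bias when follow-up is short, as the last table shows. It would be wrong to say that the design offers no protection. But 6.2 names ordinary logistic and Cox regression and describes no conditioning on patient, so that protection cannot be assumed, and it disappears as follow-up approaches 11 years.

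Fourth, 3.1 bases confounder selection on theory or literature, and its list includes immunocompromising comorbidities that 6.2 omits. The set may therefore not be closed, and an analysis plan could add year. Even so, both sections name season as the calendar-time term.

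One further inference should be resisted: that risk-factor codes are under-recorded in the early years because the data begin in 2014, and that a rerun limited to later years is needed. The protocol sets no look-back for these codes and does not say whether earlier diagnoses that are still active are missing. That would be confounder misclassification, which a year term does not repair.

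**Conclusion.** The omission is real for both models: season is the only calendar-time term, and it cannot absorb change between years. Whether this biases anything depends on joint drift in antibiotic use and UTI occurrence or recording, which the protocol does not address. Under the assumed trends and an unconditioned logistic model, the distortion is about 2% or less for moderate drift, so probably minor for all antibiotics combined. It is about 4-10%, in either direction, for a single antibiotic with a 3- to 5-fold change in use and a 1.5- to 2-fold change in recording. A within-person analysis with a few years of follow-up would bring it to about 1% or less in most of these settings. For the hazard ratios the argument is qualitative only: they use the same confounder set, and their clock is not calendar time. This is an inexpensive improvement to consider, not evidence that the planned estimates are wrong.

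**What to change.** In sections 3.1 and 6.2, replace season variability with season and calendar year. Enter year as a categorical, time-updated term in the logistic and Cox models, including the per-antibiotic models. If the analysis is carried out as a self-controlled case series, enter year as calendar-time intervals alongside season.

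Cost: 11 calendar years need 10 indicator terms per model, and intervals become slightly wider in the smallest subgroups. No new data are needed, because the dates that give season also give year. Settling this before the analysis avoids a choice made after the results are seen.
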